#### Control Condition

Although the intervention was specifically designed to deliver key BCTs, a number of BCTs are present in standard medical care and therefore also present in the control condition in this study (summarized in Table 3).

**Table 3 table3:** Description of control condition content specified in terms of the Behavior Change Technique Taxonomy Version 1 and the Mode of Delivery Taxonomy*.*

BCT^a^ and definition	Application in this study
Goal setting (outcome): The person is encouraged to set a general goal that can be achieved by behavioral means but is not defined in terms of behavior (eg, to lose weight), as opposed to a goal based on changing behavior.	All participants enrolled in the research study are encouraged to lose weight by increasing their level of physical activity and improving their diet; MOD^b^: digital, wearable, and accessory
Provide information on consequences of behavior to the individual: information about the benefits and costs of action or inaction to the individual or tailored to a relevant group based on that individual’s characteristics.	Participants in the control group attend a small group session to receive their Fitbit Flex 2. Standard advice regarding healthy diet and lifestyle is provided at this session; MOD: printed material and leaflets
Self-monitoring of behavior: establish a method for the person to monitor and record their behavior(s) as part of a behavior change strategy.	Participant is provided with a Fitbit Flex 2 activity tracker. The visual display does not provide summary data, the app interface is modified to not present summary data, and the participant is not given any method for monitoring/recording their activity level using Fitbit; MOD: digital, wearable, and accessory

^a^BCT: behavior change technique.

^b^MOD: mode of delivery.

##### Materials

All participants in the control group were provided with Fitbit Flex 2 to track health outcomes. The display panel on this device does not present summary data (ie, step count and number of active minutes), and the application dashboard was modified to not display summary data.

On being recruited to the study based on meeting the eligibility criteria (BMI ≥25 kg/m^2^), all participants were encouraged to lose weight (ie, BCT; *goal setting [outcome]*) because of health care professionals’ duty of care. Participants in the control group attended a 15-min session in small groups of 10 to 15 participants, where they received a Fitbit Flex 2. In addition, as in standard medical care, there was provision of health information at this session (ie, BCT *information on consequences of behavior to the individual*, but not BCT *instruction on how to perform the behavior* or *demonstration of the behavior*). Therefore, leaflets were made available, and standard advice was available from oncology nursing staff on request. No further information was given at this time. Finally, participants in the control group wore the Fitbit Flex 2 for monitoring their physical activity, but without *goal setting (behavior)*. The visual display on the device and the app limited but did not eliminate their ability to *self-monitor* behavior.

### Participants

#### Inclusion Criteria

Adults aged 18 to 70 years, having a calculated BMI equal to or greater than 25 kg/m^2^, with a solid cancer and who had completed cancer treatment (except for hormone therapy), attended Oncology Services in Letterkenny University Hospital during the recruitment phase, and had a willingness to use mobile technology were eligible to participate. A total of 10 eligible participants who did not own a smartphone were provided with an Amazon Fire 7 Tablet.

#### Recruitment and Consent

The clinical team identified 159 eligible participants who were identified sequentially from the oncology outpatient waiting list. The research team contacted them by telephone and described the aims and design of the study. Prospective participants who were interested in the study were sent an invitation letter, participant information sheet, and consent form. Informed written consent was provided by 123 participants (77.3% response rate) who attended baseline assessments. Participant characteristics are described in Table 4.

Of the 36 participants who did not consent to participate, 28 were not interested, 3 were waiting for surgery, 1 had chronic obstructive pulmonary disease, 1 was undergoing recurrence workup, 2 had young children, and 1 did not drive (see Figure 2).

**Table 4 table4:** Participants’ characteristics at baseline assessment.

Characteristics		Control	Intervention	2-tailed *t* test (*df*)	*P* value
Age, mean (SD)		59.24 (7.65)	55.61 (8.05)	2.39 (105)	.02
Weight (kg), mean (SD)		87.10 (16.32)	84.18 (13.98)	0.99 (105)	.32
BMI^a^ (kg/m^2^), mean (SD)		32.64 (5.41)	30.33 (3.99)	2.53 (105)	.01
Gender, female:male		49:4	42:12	—^b^	—
**Have you ever been told by a doctor that you have or have had any of the following conditions?, n (%)**					
	Angina	1 (1.9)	2 (3.7)	—	—
	Heart attack	3 (5.7)	1 (1.9)	—	—
	High blood pressure	19 (35.8)	18 (33.3)	—	—
	Stroke	3 (5.7)	1 (1.9)	—	—
	Diabetes	5 (9.4)	6 (11.1)	—	—
	High cholesterol	21 (39.6)	20 (37.0)	—	—
	Depression	12 (22.6)	9 (16.7)	—	—
	Anxiety	12 (22.6)	12 (22.2)	—	—

^a^BMI: body mass index.

^b^Not applicable.

#### Sample Size

The statistical program G*Power was used to conduct power analysis. With 2 groups (intervention and control), 3 measurements (baseline, time 1, and time 2), an assumed correlation among repeated measures of 0.3, and a small-medium effect size and a power of 0.8, the recommended sample size for repeated measures analysis of variance (ANOVA) was 102. Sample size calculations were made considering attrition rates (approximately 20%) observed in similar studies using mobile technology interventions with cancer survivors [24].

### Procedure

A flow diagram of the progress through each phase of this 2-group parallel randomized trial is presented in Figure 2. A total of 123 eligible participants attended baseline assessments. Participants were randomized to the control or intervention arm. Of 123 participants, 62 assigned to the intervention group were invited to attend a lifestyle information and education session where they would also receive their Fitbit activity monitor, and 55 were able to attend. During the lifestyle information and education session, each participant was provided with a Fitbit Alta. The Fitbit activity tracker was set up and paired with the participants’ mobile device. The participant was given an information sheet with instructions on how to synchronize their Fitbit device and app and asked to perform this weekly.

The remaining 61 participants assigned to the control group were invited to an appointment where they would be provided with a Fitbit activity monitor, and 53 were able to attend. During this meeting, each participant was provided with a Fitbit Flex 2. The Fitbit was paired with the participants’ mobile device. The participant was given an information sheet with instructions on how to synchronize their Fitbit and asked to perform this weekly or at least once a month to prevent loss of data.

All participants wore a Fitbit® activity monitor for the 6-month duration of the study. Participants in the intervention group received weekly personalized SMS text messages, including feedback on their physical activity level and a personalized physical activity goal each week for 8 weeks.

All participants were invited to a postintervention assessment (12 weeks later) to determine efficacy of the lifestyle information and education session and personalized goal setting mHealth intervention for increasing physical activity and improving clinical and psychological outcomes.

All participants continued to wear Fitbit for the remainder of the study, but the personalized goal setting intervention had ceased after 12 weeks. To determine if any effects of a lifestyle information and education session and personalized goal setting mHealth intervention were maintained 3 months later, all participants were invited to a follow-up assessment (6 months after baseline assessment).

At the conclusion of the study, all participants in the intervention group were invited to be interviewed about their experience of the Moving On program, and 13 interviews were conducted.

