## Methods

### Study Design

A 2-arm, parallel, open-label RCT design was used to investigate the impact of a personalized mHealth intervention versus standard care on primary and secondary health outcomes. Eligible participants were randomized to either the intervention or the standard care control condition using a computerized random number generator. Assessments took place before randomization (T0; baseline), at 12 weeks (T1; intervention end), and at 24 weeks (T2; follow-up). The study was not blinded.

On completion of the study, a series of semistructured interviews were carried out to assess retrospective acceptability of the intervention from the perspective of the recipients. Purposeful maximum variation sampling was used. The theoretical framework of acceptability of health care interventions was used as a topic guide [22]. Specifically, open-ended questions were asked regarding participant’s affective attitude toward the intervention, the intervention’s coherence, participant burden, perceived effectiveness, and participants’ sense of self-efficacy.

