##### Lifestyle Information and Educational Session (Week 1)

Participants in the intervention group attended a 1-day (4-hour) session in small groups of 10 to 15 people, where they received personalized and tailored lifestyle information from physiotherapists, a dietician, a clinical psychologist, and a behavioral scientist. Participants received a comprehensive presentation from each specialist. The physiotherapists demonstrated a series of daily strengthening exercises that were suitable and safe posttreatment. Moderate physical activity for 30 min 6 days a week, 45 min 4 days a week, or 10 min 2 times a day was recommended. Participants were advised to choose a personal activity schedule that best fit their lifestyle. Their preference or adherence to a particular schedule was not measured or controlled. The behavioral science researcher prescribed a weekly increase of 10% in average daily step count over the course of the program. The dietician advised participants to reduce their calorific intake, reduce red meat, processed meat, salt and sugar, and increase fruit, vegetable, and fiber intake. Participants were provided with an information sheet to take home summarizing the key messages from the lifestyle information and education session and booklets by the World Cancer Research Fund on healthy eating and physical activity. The BCTs included in this session are shown in Table 1.

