### Outcomes

The outcomes measured at baseline (T0), 12 weeks (T1; intervention ends), and 24 weeks (T2; follow-up) are described below.

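### The step tracker is issued only after randomization, at arm-specific sessions, so step count has no T0 value and 15 of 123 randomized people have no documented route to a device

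*Protocol article*

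**What the plan says.** Study Design places the T0 assessment before randomization, and Procedure gives the same order: "A total of 123 eligible participants attended baseline assessments. Participants were randomized to the control or intervention arm".

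The device comes later. The 62 people allocated to intervention were invited to a "session where they would also receive their Fitbit activity monitor, and 55 were able to attend"; the tracker handed out there was the Alta model. The intervention description makes this a 4-hour session in week 1. The 61 controls were asked to come to an appointment "where they would be provided with a Fitbit activity monitor, and 53 were able to attend", which the control Materials section describes as a 15-minute group session.

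Three other statements bear on this:

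- Outcomes opens with "The outcomes measured at baseline (T0), 12 weeks (T1; intervention ends), and 24 weeks (T2; follow-up) are described below". The list below it includes objective activity (average daily step count), recorded continuously by the Fitbit.
- Procedure states "All participants wore a Fitbit® activity monitor for the 6-month duration of the study".
- Statistical Analysis aims at intention-to-treat through imputation. It compares step count by an independent-samples t-test over the 24 weeks, while the other measures get a 3 × 2 mixed ANOVA that includes baseline.

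**The concern.** A measure that depends on a device handed out after allocation cannot have a value from before allocation. Whether a person has the measure at all depends on attending a session that is itself post-randomization and differs in burden between arms (4 hours against 15 minutes).

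Step count is the device-measured behavior outcome and the direct target of the goal-setting component. If the report repeats that it was measured at T0, on all participants, under intention-to-treat, it will claim three properties that the described procedure does not give this outcome. It is also analyzed without any baseline term. Table 4 shows the arms differing at baseline in age (59.24 v 55.61 years, P=.02) and BMI (32.64 v 30.33 kg/m², P=.01). With no T0 steps, nobody can check directly whether the arms already differed in walking.

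**Working it through.** **Order of events.** T0 assessment of 123 → randomization (62 and 61) → arm-specific session → device issued → recording starts. The Fitbit is the only step source, and no run-in wear or other issue route is described. So no T0 step count can exist under this procedure. Recording in the intervention arm begins at or after the education session.

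**Who has a device by the described route** (counts from Procedure).
- Intervention: 62 − 55 = 7 without; 7/62 = 11.3%
- Control: 61 − 53 = 8 without; 8/61 = 13.1%
- Total: 7 + 8 = 15; 15/123 = 12.2%; with a device at most 55 + 53 = 108

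Table 4 points the same way. Its gender counts are 49 + 4 = 53 controls and 42 + 12 = 54 intervention participants, 107 in all (t tests on 105 df), although 123 attended baseline. The one-person gap between 107 and 108 is not explained.

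**The plan's own sample size.** The stated 102 is for a repeated measures ANOVA. With alpha 0.05 and sphericity (both assumed), 2 groups, 3 measurements, correlation 0.3 and power 0.8, it reproduces at f = 0.15 for the within or interaction effect. It was not derived for the step-count t-test, and this point does not depend on it.

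**Precision of the step t-test** (noncentral t, two-sided 0.05).

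| Analyzed | Detectable d at 80% power | Power at d = 0.5 |
|---|---|---|
| 123 (61 + 62) | 0.509 | 78.5% |
| 108 (53 + 55) | 0.544 | 73.0% |

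**What a step baseline would have added.** A covariate with correlation r to the outcome multiplies the detectable d by √(1 − r²). The documents give no such r for steps, so the range is an assumption. With 108 people:
- r = 0.5: 0.544 × 0.866 = 0.47
- r = 0.7: 0.544 × 0.714 = 0.39
- r = 0.8: 0.544 × 0.600 = 0.33

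**Selection by attendance.** If non-attenders in an arm walk D steps/day less than attenders, the attender mean exceeds the whole-arm mean by (share not attending) × D. With an assumed D = 2,000:
- deficit in the intervention arm only: 7/62 × 2,000 = 226, so the arm difference is raised by about 226 steps/day
- deficit in the control arm only: 8/61 × 2,000 = 262, so it is lowered by about 262
- same deficit in both arms: 226 − 262 = about −36

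The documents do not say which case applies, so the direction is unknown.

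**The case against.** The Outcomes lead-in is generic. It also covers the acceptability ratings, which nobody could give before receiving the intervention. Step count has its own timing (continuous) and its own analysis (a between-arm test over the 24 weeks), and no change-from-baseline step analysis is planned. This stands in part: the lead-in is loose wording rather than a planned T0 step analysis, but as written it is still wrong for steps.

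Four stronger readings are tempting, and the documents do not support them:

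- *The missing T0 value biases or prevents the comparison.* It does neither. A comparison of randomized arms after allocation needs no baseline, and intervention-arm steps recorded after the education session reflect the effect under study.
- *Prior activity cannot be adjusted for.* The Godin questionnaire and the 6-minute walk test are both T0 measures. What is lost is a step-based covariate.
- *The 15 certainly have no step data.* The article says who attended, not that the others were never given a device later. The participant flow figure, which carries an intention-to-treat label, is not available here. What can be said is that no other route is described.
- *The 4-hour session inflates the arm difference by some 225 steps/day.* That needs a deficit in one arm only. Non-attendance was similar and slightly lower in the 4-hour arm, and an equal deficit in both arms gives about −36. Similar rates do not, however, show that similar people were lost.

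The imputation plan is also a fair reply on intention-to-treat, but for these 15 it would have no observed step value, before or after randomization, to work from.

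**Conclusion.** The point holds as a mismatch between what is stated and what the procedure can deliver for one outcome. Step count has no pre-randomization value, and 15 of 123 randomized people (12.2%) have no documented route to a device. An intention-to-treat step result would rest wholly on imputation for them; without imputation it compares at most 108 attenders.

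The sample loss is modest in power terms: the detectable d rises by 0.035, and power at d = 0.5 falls by 5.5 percentage points. Beyond that, the trial gives up a step-based baseline check and covariate, and leaves open selection by attendance of unknown direction and size. No bias is demonstrated. The conclusion assumes that the article describes every route by which a tracker was issued.

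**What to change.** **At design stage.** Issue and pair a tracker with masked display and dashboard at the existing T0 visit, which all 123 attended. Record a short period, such as 7 days, and then randomize. Let people who miss their session keep the device, and use the baseline mean as covariate in the step analysis. This gives a T0 value and removes attendance as the gate. No new visit is needed, and the control arm already used a masked set-up. The costs are about a week's delay to randomization, extra masked devices for the intervention arm, some reactivity to being monitored (the article concedes that masking did not remove self-monitoring entirely), and a different device model for intervention non-attenders than for attenders.

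**Now.** The article reports data collection complete and analysis underway, so the remedy is in the text and the analysis:

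- Remove step count from the outcomes said to be measured at T0.
- Reconcile the statement that all participants wore a tracker with 55 + 53, and say what happened to the other 15.
- Report the step analysis as covering those issued a device (at most 108), and do not call it intention-to-treat unless all 123 are truly included.
- Adjust the step comparison for the T0 Godin score and 6-minute walk distance, fixing this before step results are seen by arm.

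These changes need no new data. Their cost is a few edited sentences and a regression model in place of the t-test.

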**Figure 2 figure2:**
[figure not shown]
Flow of participants through each stage of the current randomized controlled trial. BMI: body mass index; ITT: intention-to-treat; SMS: short message service.

### Outcomes

The outcomes measured at baseline (T0), 12 weeks (T1; intervention ends), and 24 weeks (T2; follow-up) are described below.

#### Clinical Outcomes

##### Anthropometric Measurements

Weight was measured in light clothing without shoes in kilogram plus 2 decimal places using a calibrated Seca scale. Height was recorded without shoes in centimeters plus 2 decimal places using a stadiometer. BMI was calculated using weight and height. Waist circumference was measured at the halfway point between the hip bone and lowest rib using a stretch-resistant measuring tape [25]. To standardize measurement, one set of scales and stadiometer were used on all participants at each assessment.

##### Functional Exercise Capacity

The 6-min walk test is a clinical exercise test that measures the distance walked in 6 min on a hard, flat surface. Systolic blood pressure, diastolic blood pressure, heart rate, blood oxygen saturation, subjective fatigue, and dyspnea were measured pretest, posttest, and 4 min later.

#### Psychological Outcomes

Medical Outcomes Survey Short Form (RAND36) [26] is composed of 36 items, measuring 8 individual subscales that represent 3 general areas of health-related quality of life: physical, emotional, and social well-being. The subscales include physical functioning, role function–physical (role limitations caused by physical factors), role function–emotional (role limitations caused by emotional factors), bodily pain, social functioning, emotional well-being, energy/fatigue, and perceived general health. Each subscale is standardized on a scale from 0 to 100, with higher scores indicating better functioning.

The Three-Item Loneliness Scale [27] consists of 3 questions such as “How often do you feel that you lack companionship?” The responses are coded 1: hardly ever, 2: some of the time, and 3: often. Scores range from 3 to 9, with higher scores indicating greater loneliness.

The Brief Fatigue Inventory [28] comprises 9 items measured on a 10-point Likert scale. The scale is composed of 2 subfactors that assess the severity of fatigue and its effects on the respondent’s ability to perform activities of daily living. Scores range from 0 to 90. Higher scores represent worse self-reported fatigue.

The General Self-Efficacy Scale [29] is a 10-item measure with answers ranging from *not true at all* to *exactly true*. It assesses the participants’ belief in their ability to succeed in certain situations. Scores range from 10 to 40, with higher scores indicating higher self-efficacy.

Exercise self-efficacy was assessed using a 4-item measure developed in a previous study by Armitage [30]. Items were as follows: “To what extent do you see yourself as being capable of participating in regular physical activity? incapable–capable”; “How confident are you that you will be able to participate in regular physical activity? not very confident–very confident”; “I believe I have the ability to participate in regular physical activity. definitely do not–definitely do”; and “How much personal control do you feel you have over participating in regular physical activity? no control–complete control. Items were measured using 7-point scales.

Social support for physical activity was measured using a 3-item measure developed by Molloy et al [31] that was based on an earlier measure [32]. The items began with the stem “In the last week I...had somebody to encourage me to participate in physical activity on a regular basis,...had somebody to participate in physical activity with me,...felt supported in having a regular pattern of physical activity.” The responses to the 3 items were on a 7-point scale and ranged from 1: disagree to 7: agree.

#### Health Behavior Outcomes

Self-reported physical activity level was measured using the 4-item Godin Leisure-Time Exercise Questionnaire [33]. Respondents rate the frequency of 15-min bouts of strenuous, moderate, and mild exercise in a 7-day period. Participants also rate how often they engage in regular activity sufficient to break a sweat (1 often, 2 sometimes, and 3 never). Higher scores indicate higher subjective physical activity.

Objective physical activity level (ie, average daily step count) was measured continuously using the Fitbit activity tracker.

Dietary data were collected using the European Prospective Investigation into the Cancer and Nutrition (EPIC) Norfolk Food Frequency Questionnaire (FFQ) [34]. Participants were asked to report the frequency of 130 different foods and beverages consumed over the previous 3 months. The FFQ EPIC Tool for Analysis [35] provides estimates of 10 food groups.

